### Formative and summative evaluation

#### Overview

We will use mixed methods to conduct both formative and summative evaluations. These evaluations will support identification and addressing of implementation barriers in real time and will also be used to assess both implementation (reach, adoption, implementation, and maintenance) and effectiveness outcomes. The following data sources will be used: (1) surveys of staff and clinic leaders; (2) qualitative data from formative and summative evaluation activities throughout the implementation period, including interviews and participant observation of all implementation meetings between the practice coach and LIT, (3) patient-reported data (PROs) on alcohol use, receipt of alcohol-related care, and ART adherence, and (4) quantitative EHR data that measures receipt of alcohol-related care and HIV-related clinical outcomes including HIV viral load. The alcohol biomarker phosphatidyl ethanol (PEth) is collected by dried blood spot. Study outcomes are summarized in Table 3 below.

#### Data sources, collection, and measures

##### **Surveys of staff and clinic leaders**

During the pre-implementation phase, we will conduct surveys with clinic staff at each site to gather baseline information about their current alcohol care practices and tailor the practice facilitation intervention to their local context. Surveys will be administered electronically via REDCap during the pre-implementation phase [50, 51]. These surveys will comprise both structured and open-ended questions, aimed at understanding the staff’s knowledge, attitudes, beliefs, and practices.

##### **Qualitative data from formative and summative interviews and observations**

We will conduct semi-structured qualitative interviews during both the pre-implementation (formative) and sustainment (summative) phases with staff members from participating clinics. During the pre-implementation phase, we will ask about the staff’s experiences with alcohol EBIs, clinic processes, and clinical cultures. In the sustainment phase, semi-structured interviews will focus on clinic staff’s experiences with the clinical and implementation intervention and perspectives on needed supports to sustain stepped care and preferences for person or computer-delivered intervention. At both stages, we will employ a combination of purposive and snowball sampling informed by the LIT to identify potential interview participants, including individuals in clinical, administrative/support, and leadership roles. LIT teams will send recruitment emails to all eligible providers at their clinics and introduce the study/interview recruitment at onsite meetings, attended by clinic staff, to elicit interest equally across all providers. Snowball sampling will be used to identify potential participants that may have important perspectives and need additional recruitment outreach. The study team will also regularly review interview recruitment progress to assess for missing perspectives and will work with LIT teams to adjust recruitment strategies as needed. We anticipate reaching thematic saturation with a sample size of 21–30 participants (7–10 from each clinic). Potential interviewees will be identified and scheduled for phone interviews conducted by trained study staff. At the start of each interview, participants will be asked to provide verbal consent. The interviews, lasting approximately 30–45 min, will consist of open-ended questions and semi-structured follow-up questions guided by the domains of the CFIR. For sustainment period interviews, we will follow the same interview recruitment and data collection procedures described above with the goal of recruiting 5–7 clinical staff and 5–7 patients per site.

For patient interviews, LIT research staff will approach eligible patients after in-clinic visits to elicit interest in interview participation. Content will include experiences with intervention participation and explore preferences person or computer-delivery. Patients who agree to participate in a 60-minute study interview will then be contact via email to schedule the interview. All interviews will take place virtually, via the online platform Zoom, and participants will receive $75 as compensation for participating in this component of the study.

During the entire study period (pre-implementation, implementation, sustainment), we will conduct ***participant observation*** of all implementation meetings between the Practice Coach and LITs and clinic representatives. Similar to our prior studies [30, 52, 53], a trained qualitative researcher will take verbatim ethnographic fieldnotes of discussions that happen during implementation meetings. We will then use structured templates to summarize observed meeting data by site. Iterative summaries will be generated to identify barriers and facilitators by site, address barriers (e.g., staff turnover) and capitalize on facilitators (e.g. change in practice facilitator skills) in real time, and to assess implementation outcomes [54].

##### **Patient-reported data through the CNICS PRO**

Data on self-reported alcohol use (AUDIT-C, AUDIT, MINI) [38, 40, 55, 56], receipt of alcohol-related care (Treatment Service Review), and ART adherence (Self-rating and Visual Analog Scale) [57–61] will be extracted from the PROs. Specific to this implementation study, we have added an additional PRO question asking patients if they received an alcohol intervention since their last visit.

##### **Biomarkers**

Using dried blood spot collection, we will measure an alcohol biomarker, PEth. Because PEth is not part of routine care, participants will be compensated $10 for this procedure [43, 62].

##### **EHR data**

We will collect patient demographics, HIV1-RNA, CD4 cell count, and alcohol pharmacotherapy prescription from the EHR using the CNICS data collection infrastructure [36].

##### Study outcomes

Our study outcomes, guided by RE-AIM, are described in Table 3 below.

**Table 3 Tab3:** Study outcomes using the RE-AIM framework

Dimension	Exemplar Use Defined by NCI	Present Study Measure
**R**each	• Percent of individuals who participate, among all patients	Percent of patients with UAU who receive an alcohol EBI
	• Characteristics of participants compared to non-participants or to target population	Above measure compared across racial/ethnic groups, gender, and clinical characteristics
**E**ffectiveness	• Measure of primary or broader outcomes	1) Reduced UAU (AUDIT-C score < 3/4 women/men)* 2) Viral suppression (HIV-RNA < 200) 3) ART adherence (> 90%) 4) PEth
**A**doption	• Use of qualitative methods to understand adoption at setting level • Use of qualitative methods to understand staff participation	Barriers and facilitators to delivering alcohol EBIs, intervention components important to enhancing delivery and site preferences related to selection of computer or person delivered intervention.
	• Percent of staff invited that participate	1) Provider report of delivering alcohol EBIs 2) Percent of providers prescribing AUD pharmacotherapy among all clinic providers
**I**mplementation	• Percent of intervention delivery or calls completed, etc. (e.g., adherence or consistency)	1) Percent of patients reporting receiving an alcohol intervention since their last visit among all responding to the PROs 2) Percent of alcohol treatment sessions completed
**M**aintenance	• Measure of primary outcome (with or without comparison to a public health goal) at ≥6mo follow-up after final intervention contact	Percent of patients reporting receiving an alcohol intervention in the past six months among all responding to PROs at six months post final contact with Practice Coach

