**Methods:**

Guided by the Consolidated Framework for Implementation Research and Reach, Effectiveness, Adoption, Implementation and Maintenance frameworks, we will conduct a Hybrid Type 3 effectiveness-implementation study testing whether external practice facilitation increases reach, adoption, implementation, and maintenance of stepped care for UAU in three Center for AIDS Research (CFAR) Network of Integrated Clinical Systems (CNICS) HIV clinics in the United States. We will secondarily test whether practice facilitation is associated with clinical outcomes. We will first conduct a mixed methods formative evaluation to tailor delivery of practice facilitation (including the tools, technical assistance, and content expertise offered) based on each site’s context and needs (Aim 1). We will then deliver practice facilitation across the three sites sequentially to implement a stepped-care model of alcohol treatment to patients with UAU. Stepped care, where non-responders to alcohol EBIs are offered a more intensive therapy, will specifically include person- or computer-delivered brief alcohol intervention, on-line cognitive behavioral therapy, and linkages to alcohol pharmacotherapy. Clinical outcomes will include: (1) clinic-level implementation outcomes of stepped care EBIs for alcohol use including reach, adoption, maintenance, using mixed methods (Aim 2a) and (2) patient-level outcomes using interrupted time series analysis with synthetic controls (Aim 2b). Finally, we will use summative evaluation to describe barriers and facilitators to implementation of the interventions at each site to describe maintenance and inform widespread sustainable implementation (Aim 3).

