Implementation of EBIs for UAU in clinical settings is challenged by provider- and clinic-level barriers including lack of time and resources, inconsistent screening, inadequate training in managing UAU, operational workflows, and low confidence in the use of alcohol pharmacotherapy [24]. Practice facilitation is a multilevel intervention implementation strategy that addresses barriers to implementation of evidence-based practices. With practice facilitation, a practice coach offers tools, resources, hands-on guidance, and content expertise to assist the team in developing strategies to successfully implement an evidence-based practice [25–27]. Support by a practice coach is provided in near-real time and optimized by relationship development with each clinic site. There is substantial evidence in favor of practice facilitation in primary care, and multiple studies are using practice facilitation to implement alcohol EBIs [23, 25, 27–30]. Based on evidence in primary care settings [31, 32], practice facilitation for implementing alcohol EBIs may hold great promise for improving access to care in HIV clinics.

We are conducting a novel study in HIV clinics in which we will test practice facilitation to implement stepped care for UAU. In this manuscript, we describe the protocol of our Hybrid Type 3 effectiveness-implementation study guided by the RE-AIM (Reach, Effectiveness, Adoption, Implementation and Maintenance) evaluation framework [33]. Our study tests whether external practice facilitation increases reach, adoption, implementation, and maintenance of stepped care for UAU (our clinical intervention) in three Center for AIDS Research (CFAR) Network of Integrated Clinical Systems (CNICS) HIV clinics. We will secondarily test whether practice facilitation is associated with decreased UAU and improved ART adherence and viral suppression at the patient level (**e**ffectiveness). Formative and summative evaluations – guided by the Consolidated Framework for Implementation Research (CFIR) [34] - will also be used to tailor the implementation supports provided throughout the trial and characterize barriers and facilitators to implementation.

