## Reach and effectiveness evaluation (clinical measures of UAU and HIV care, Aim 2b)

Reach and Effectiveness will be assessed using an interrupted time series with synthetic control to evaluate whether practice facilitation is associated with our primary implementation outcome (percent of patients reporting receiving an alcohol intervention since their last visit among all responding to PROS across all CNICS sites) and with our secondary effectiveness outcomes (alcohol use, ART adherence, and viral suppression) [67, 68].

An interrupted time series design allows for conducting a rigorous naturalistic study, results can be displayed graphically to intuitively represent findings, historical trend is accounted for in the analytic model, and the size of the effect can be estimated at different times post intervention dissemination [69–71]. Addition of synthetic control can improve estimation of the counterfactual condition in which the intervention was not added to the specific HIV clinics by reducing selection bias and satisfying the parallel trends assumption, which is needed for controlled interrupted time series analyses [69].

The sample will include all patients with UAU seen at each of the CNICS sites during the study. The CNICS sites that did not have the intervention will be the control sites for the interrupted time series with synthetic control. The outcomes will be expressed as a proportion per month. Therefore, the denominator for all outcomes is all patients with UAU with a visit to the participating CNICS clinics for each month of the study period. Numerators for the effectiveness outcomes are defined as follows: (1) Implementation based on patient report (primary outcome); (2) AUDIT-C score ≤ 3 women and ≤ 4 men; (3) viral suppression as indicated by HIV RNA ≤ 200 copies; and (4) high adherence to ART defined as 90% on the visual analog scale.

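### Maintenance is claimed as a tested increase, but it is defined as one percentage with no stated comparator and is not tied to the controlled time series

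*Protocol article*

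**What the plan says.** The Background of the protocol article states the aim in causal terms: "Our study tests whether external practice facilitation increases reach, adoption, implementation, and maintenance of stepped care for UAU". The abstract and the Discussion make the same claim.

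Table 3 (Study outcomes) gives the Maintenance measure as the percentage of patients who report an alcohol intervention "in the past six months among all responding to PROs at six months post final contact with Practice Coach". The row names no reference value, earlier time point or control group.

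The abstract places maintenance among the "clinic-level implementation outcomes of stepped care EBIs for alcohol use including reach, adoption, maintenance, using mixed methods (Aim 2a") and has Aim 3 describe it through the summative evaluation.

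The Aim 2b section opens with "Reach and Effectiveness will be assessed using an interrupted time series with synthetic control". It names a primary implementation outcome, "percent of patients reporting receiving an alcohol intervention since their last visit among all responding to PROS across all CNICS sites", and three secondary outcomes: alcohol use, ART adherence and viral suppression. Maintenance is not named. The CNICS clinics without the intervention serve as controls, and outcomes are monthly proportions over a study period whose end is not given.

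**The concern.** A claim that facilitation increases maintenance needs something to compare with: the level without facilitation, and ideally the level when facilitation ended. A single percentage at a single time supplies neither. If alcohol care changes across the network for other reasons, that change is part of the figure. If delivery decays once the coach leaves, one late reading does not show it.

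The article treats secular trend as a real threat. It uses synthetic controls, site-specific slopes and a staggered roll-out against it for the primary and effectiveness outcomes, but ties none of these to Maintenance. At stake is whether the study can say that stepped care lasted because of facilitation, which is one of its named aims.

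**Working it through.** The plan states no figure for Maintenance that could be reproduced. The only power statement (Power considerations) concerns trend change and gives no alpha, power or number of time points. The check is therefore a comparison of the text, calendar arithmetic and a labelled illustration.

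1. **Claim against method.**
   - Background, abstract and Discussion: a test of an increase in maintenance.
   - Table 3: one percentage, one time point, no comparator.
   - Abstract: mixed methods (Aim 2a) and description (Aim 3).
   - Aim 2b: a controlled analysis whose named outcomes omit Maintenance.

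   Read together, the claim is causal and the assigned method is descriptive.

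2. **When Maintenance is read.** Inputs from the section on the implementation strategy: 18 months of facilitation per clinic (3 + 12 + 3), with starts about 12 months apart. Assume that final contact falls at the end of the 18 months.
   - Site 1: 0 + 18 + 6 = month 24
   - Site 2: 12 + 18 + 6 = month 36
   - Site 3: 24 + 18 + 6 = month 48

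   Each reading comes 24 months after that site's start, and the three are spread over 48 − 24 = 24 calendar months.

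3. **What secular change would do.** The documents give no rates and no drift, so the following is illustration only. Drift over 24 months = 24 × monthly drift: 24 × 0.1 = 2.4 points, 24 × 0.25 = 6 points, 24 × 0.5 = 12 points. Suppose a site stands at 20% before facilitation and 35% at the Maintenance assessment. A site-only contrast is 35 − 20 = 15 points whatever the drift. The controlled contrast is 15 − drift, giving 15, 10, 5 or 0 points when the controls move by 0, 5, 10 or 15 points.

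4. **What is available to correct it.** CNICS has ten clinics (Implementation context), so up to 10 − 3 = 7 can act as controls. The primary outcome is nearly the same patient report, summarised monthly across all CNICS sites. The Aim 2b section says that effects can be estimated at different times after the intervention, and it gives each site its own slope after the intervention relative to its synthetic control. It does not say whether the series reaches months 24, 36 and 48.

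5. **Recall period.** The PRO item added for this study asks about the time since the previous visit (Patient-reported data through the CNICS PRO), while Maintenance uses a six-month recall. PROs come about every six months. A patient answering m months after final contact, with a six-month interval, has (6 − m)/6 of the recall period before final contact: 5/6 at m = 1, 1/2 at m = 3, 0 at m = 6. Averaged over m = 1 to 6, this is (5 + 4 + 3 + 2 + 1 + 0)/36 = 15/36, or about 42%. Early answers therefore partly describe care given while the coach was still active.

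**The case against.** The strongest reply is that Table 3 lists measures, not analyses. Its Implementation row is an equally bare percentage, yet the Aim 2b section analyses that measure with synthetic controls although it opens by naming only Reach and Effectiveness. Silence in the Maintenance row therefore does not prove an uncontrolled analysis, and a condensed article may leave the estimation to a fuller document. This stands. It rules out saying that Maintenance will certainly be analysed without controls. It does not remove the mismatch in what is printed: the article brings the Implementation measure into the controlled analysis explicitly, and gives Maintenance a different method.

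A second reply is that the framework exemplar in Table 3 allows the outcome "with or without comparison to a public health goal) at ≥6mo follow-up after final intervention contact", so a single follow-up percentage conforms to it. It does, as a description. Conforming to the exemplar does not support a claim of increase.

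A reader might go further and infer that the plan as a whole cannot distinguish a sustained effect from secular change, or that control data lie unused. The documents do not support either. Control data on nearly the same measure feed the primary analysis, and if that series extends far enough it could answer the question. Nor is it the same PRO item: the recall periods differ, and fielding at the control clinics is implied by the Aim 2b section, not stated where the item is described.

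A reader might also attach a margin of error to a single month's percentage. The documents give neither respondents per month nor an expected percentage, and do not say that one month is used, so no such figure is offered here.

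**Conclusion.** The point holds in a limited form. The article claims to test an increase in maintenance, defines Maintenance as one percentage with no stated comparator, assigns it to mixed methods, and does not name it in the controlled time series. That percentage alone cannot separate a sustained effect from network-wide change. The primary-outcome series could, but the text neither states nor excludes that it runs to six months after final contact.

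The size cannot be fixed from the documents. Any network-wide change enters the uncontrolled figure one-for-one. The 2.4 to 12 points shown above rest on an assumed drift of 0.1 to 0.5 points per month and on final contact at month 18. The conclusion does not depend on those values.

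This should be changed because maintenance is a named aim and a better method is within reach. It does not affect the primary outcome.

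**What to change.** - State that the interrupted time series with synthetic control on the primary PRO measure runs through at least six months after final coach contact at each site.
- Define Maintenance as the treated-minus-synthetic gap over that post-contact window, not at a single month, and report its change since the end of facilitation. Show the gap by month as well, because early answers look back into the facilitation period.
- Align the recall period of Maintenance with the item as fielded, and use the same denominator as the primary outcome.
- Keep the raw percentage as a descriptive companion.
- If this is not done, drop the claim to test an increase in maintenance and call the outcome descriptive.

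The cost is modest extra analysis and wording. Table 3 already requires follow-up to this time point at the intervention sites. The fix depends on the added item being fielded at the control clinics over the same period, which the Aim 2b section implies and the article should confirm. The gap also carries the error of the synthetic control, so it will not necessarily be more precise than the raw percentage.

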#### Data analysis and interpretation

##### **Formative surveys**

 Survey responses gathered from clinical staff during the formative evaluation will be summarized overall and at the clinic level; cross tabs of key variables will be performed and summarized.

##### **Formative participant observations**

Participant observation notes will be analyzed using the Rapid Assessment Process described above to assess Adoption. Qualitative data will be coded using techniques from Grounded Theory and Template Analysis using CFIR domains as the analysis template and guide, as we have done in similar studies [41], and used to identify barriers and facilitators aligned with CFIR domains, address barriers (e.g., staff turnover) and capitalize on facilitators in real time, and to determine the effects of practice facilitation at sites.

##### **Formative and summative qualitative interviews**

All qualitative ***interviews*** will be de-identified, digitally recorded, and transcribed by an external source. The transcriptions will be reviewed for accuracy and analyzed using the Rapid Assessment Process [63–66]. This process will be conducted iteratively to identify emergent themes with the multidisciplinary research team, triangulate data with existing theoretical knowledge and our previous research regarding implementation of brief interventions, make mid-course corrections in data collection, and check for saturation of themes. Interviews from the summative phase will be analyzed using a combination of Rapid Assessment Process and thematic analysis and triangulated with other data sources (e.g., participant observations, survey, clinical data) to inform evaluation of Aim 2a and Aim 3.

